## Methods

### Study setting

The study will be conducted by researchers and clinicians at The University of Sydney, the Sydney Children’s Hospital at Randwick and the Children’s Hospital at Westmead.

### Participants and sample size

Ten to 12 children with epilepsy (TLE and/or GGE, aged 8 to 12 years old) will be recruited for the study. Children with TLE and GGE have been selected as ToM impairments and associated social problems have been documented in these patient groups [5–7]. ToM has not yet been studied or not been found to relate to social impairments in children with other forms of epilepsy [36]. Moreover, in a recent systematic review and meta-analysis, adults with parietal and occipital lobe epilepsy were not impaired in ToM relative to controls calling into question whether children with these conditions would have ToM deficits [36]. The sample size has been selected based on guidelines provided by Julious [37] and Whitehead [38] for conducting pilot trials. Another consideration in selecting sample size was that smaller groups have been found to be more effective and engaging than larger groups in prior ToM and social skill interventions [14, 23]. Although the intended sample size is small, the primary outcomes will be able to be addressed if just two children complete the programme, as case series require a minimum sample size of two [35]. By inviting 10 to 12 children to participate, we will start with a sample size that is 5 to 6 times greater than required for dissemination of results.

#### Eligibility criteria for children with epilepsy

Children will be considered eligible if they meet the following criteria: (i) a current diagnosis of GGE or TLE, confirmed by treating neurologists, (ii) aged between 8 to 12 years old, (iii) fluency in the English language, (iv) assessed to have a full scale intellectual quotient (FSIQ) > 70, (v) absence of major developmental/psychiatric conditions (i.e. autism), sensory/motor impairments (i.e. cerebral palsy, significant visual or hearing impairments), major neurological disorder (e.g. severe brain injury), systemic and metabolic disorders that could lead to cognitive impairment, (vi) no clinical signs of drug intoxication/drug and alcohol abuse, (vii) absence of a neurological procedure/surgery in the past 6 months, and (viii) currently controlled seizures with medication, meaning that the child has experienced a stable seizure frequency for the past 6 months, as assessed by treating neurologists at enrolment. There is no seizure frequency cutoff. Children will be excluded if they (i) are undergoing active AED changes, as this could affect seizure frequency or other aspects of the child’s functioning (e.g. reduced concentration, fatigue) and may limit their ability to engage in therapy, or (ii) are currently engaged in another form of treatment for social difficulties (individual or group therapy), as concurrent treatment may add a source of bias to results. Children who have previously attended psychology sessions, but are not currently engaged in treatment, will not be excluded and will be considered eligible for the study. All children will be instructed to continue with routine clinical care for their epilepsy during the study.

#### Eligibility criteria for investigators

Investigators from The University of Sydney who will conduct intervention and assessment sessions are psychologists and neuropsychologists who hold full registration with the Psychology Board of Australia. Investigators from participating hospitals are neurologists who will be responsible for confirming diagnosis of epilepsy, current seizure stability and completing a measure of overall epilepsy severity for each participant enrolled in the trial. All investigators will be registered with Australian Health Practitioners Registration Agency (AHRPA) in their respective professions.

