### Trial design

Pilot and feasibility study guidelines were consulted in designing and planning the study [32, 33]. The study will employ a double baseline case series design, and the intervention will be run as a single-arm open-label pilot. The framework for the study is exploratory. The decision to conduct an open-label pilot was guided by research by Leon and Davis [33], who state that open-label studies in which participants are recruited to known albeit experimental interventions with no risk of receiving placebo are best practise in pilot trials. A case series was selected over a single-case or larger scale randomised controlled trial (RCT) for feasibility, ethical and methodological reasons. Case series are increasingly used in cognitive neuropsychology and are considered more robust and generalisable than single-case designs [34, 35]. Case series involve recruiting a small sample of children to a single experimental condition and assessing individual change in performance across the course of treatment [35]. The most robust and validated method for assessing within-subject change in case series is visual analysis, a method that requires each participant to be assessed at least twice prior to starting treatment (i.e. double baseline). A double baseline approach will be achieved in the current trial by assessing children twice before treatment begins (i.e. baseline 1 and 2). This will provide a stable measure of performance before the intervention, which can be compared to performance on the same measures at post-intervention and follow-up. This approach is common in case series interventions and allows researchers to conclude with some certainty that improvements are attributable to a given treatment and not to practice effects or the passage of time [35]. A double baseline design is also required for the approach that we will use to evaluate outcomes (i.e. visual analysis, see the “Statistical methods” section for more details about this method). A larger scale RCT was not considered appropriate for the current study as this is the first time the intervention will be trialled, and it does not have known positive effects.

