
#### Secondary outcome measures

##### Theory of Mind (ToM)

The strange stories task [47] will be used as the primary measure of change in ToM. Parallel versions of the task will be administered to children at baseline 1, baseline 2, post-intervention and follow-up. The strange stories task contains 12 social stories in which there is a discrepancy in characters’ perspectives or beliefs and children must explain the discrepancy with reference to characters’ thoughts and feelings. Responses are scored on a 3-point Likert scale (0 = no reference to thoughts and feelings, 1 = reference to thoughts or feelings, 2 = reference to thoughts and feelings). A single total ToM score is generated by summing items (range = 0 to 24). Three control stories from the strange stories task that are comparable in length and difficulty, but contain no reference to thoughts or feelings of characters, will also be administered to obtain a measure of general story comprehension (range = 0 to 6). The strange stories task was selected as empirical studies have found that children with GGE and TLE have significant impairments on this task [6, 7]. An additional (secondary) measure of change in ToM will be obtained with the Theory of Mind Inventory (TOMI) [48], which will be completed by parents at the same 4 time points. The TOMI is a 42-item parent-report questionnaire that assesses ToM in children aged 3 to 17 years old. Parents rate how accurate statements are for their child on a 5-point Likert scale (1 = definitely not true to 5 = definitely true), and scores are summed to generate a total raw score (range = 42 to 220), which is converted into a percentage total score (range = 0 to 100). The TOMI is being included as it has been found to be sensitive to change following interventions in other clinical populations [48].

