### Data collection and data management

The intervention and assessments will be conducted by psychologists and neuropsychologists who are trained and experienced in administering the tasks included in the assessment battery and intervention sessions. Thus, no additional training will be required for any of the investigators. To promote participant retention and completion of follow-up, home visits will be offered for assessments, as this has been found to almost double retention rates in pilot studies [58]. Home visits will not be offered for intervention sessions, as being exposed to treatment in a different learning environment may add a source of bias to results. Participants who discontinue or withdraw prior to completion of the study will not be required to complete any further assessments, as per requirements of the governing ethics committee. It is not anticipated that participants could deviate from the study protocol in any way other than discontinuing sessions.

Each participant will have a unique identification (ID) code assigned to them at the start of the study, which will be used to de-identify data and link information collected on paper and in electronic forms. During the study, de-identified data will be stored securely in the original paper and electronic copies in locked filing cabinets and password-protected files, respectively, at The University of Sydney. Codes and consent forms will be stored separately to the files themselves in a separate locked filing cabinet. After completion of the study, all data will be converted to secure electronic files and stored in password-protected files at The University of Sydney. Data will be retained until participants are 25 years of age or for a minimum of 15 years (whichever is later) as per the Australian Code for the Responsible Conduct of Research [59]. Data will only be accessible to study investigators listed on the ethics application. There are no external sponsors or other involved parties that will have access to data.

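### The main ToM measure is a rated verbal task, assessed at known visits by the team that delivers the training, so unmasked scoring could bias the ToM part of the progression rule upwards

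*Protocol article*

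**What the plan says.** All references are to the protocol article.

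- **Design.** Under Trial design, "the intervention will be run as a single-arm open-label pilot". There is no control group.
- **Staff.** Under Eligibility criteria for investigators, "Investigators from The University of Sydney who will conduct intervention and assessment sessions are psychologists and neuropsychologists". Data collection and data management repeats it: "The intervention and assessments will be conducted by psychologists and neuropsychologists".
- **Measure.** Under Secondary outcome measures, Theory of Mind (ToM), "The strange stories task [47] will be used as the primary measure of change in ToM". The child explains 12 stories, and each explanation is rated "0 = no reference to thoughts and feelings, 1 = reference to thoughts or feelings, 2 = reference to thoughts and feelings", giving a total of 0 to 24. The parent-rated TOMI is an additional measure.
- **Timing.** "Parallel versions of the task will be administered to children at baseline 1, baseline 2, post-intervention and follow-up". Procedure for intervention delivery and assessments makes these one-to-one sessions with an investigator. The post-intervention session falls on the last day of the intervention.
- **Use.** Overall success of the intervention treats scores above the mean of the two baselines as a positive trend and scores fluctuating around that mean as neither positive nor negative. No numerical margin is given. A positive trend in at least 50% of participants is sufficient to continue, with or without modification. Going ahead unmodified requires positive trends on both ToM and social competence, and every primary feasibility outcome met.

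**The concern.** Rating whether an explanation refers to thoughts, feelings or both leaves some room for judgement in borderline answers. A scorer who has helped to deliver the training, or works alongside those who did, and who knows an answer was given after it, may resolve borderline answers upwards without meaning to. The Intervention section adds to the risk: the training scenarios are drawn from this same task, and the thinker and feeler roles correspond to the two elements that the scoring key rewards.

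The stated safeguards address other threats. The double baseline is offered against practice effects and the passage of time, but a scoring shift that begins only after training appears in neither baseline. Parallel versions limit recall of particular stories; they do not hide the visit.

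At stake is the ToM half of the trend criterion. With no minimum change set, a small systematic shift could make an ineffective programme look promising on ToM, or mask a decline.

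**Working it through.** The protocol gives no SD, effect size or error rate for this rule, so there is no stated figure to reproduce. The check asks how far a modest scoring drift could move the rule.

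**Inputs from the document:** 10 to 12 children; score range 0 to 24; two baselines averaged; threshold of at least 50% of participants, so 5 of 10 or 6 of 12.

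**Assumptions:** no true change; independent children; within-child SD *s* of one administration 2 points (range 1.5 to 3); drift *d* = 1 point at the later visits, equal to one story of the 12 scored one step higher.

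**Reading A: one post score against the baseline mean, continuous scores.** The difference has variance *s*² + *s*²/2 = 1.5*s*², so its SD is *s*√1.5. The per-child chance of a positive result is Φ(*d* / (*s*√1.5)), and the number of positive children is binomial.

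| *s* | *s*√1.5 | Per child, *d* = 1 | At least 6 of 12 | At least 5 of 10 |
|---|---|---|---|---|
| 1.5 | 1.837 | Φ(0.544) = 0.707 | 0.966 | 0.958 |
| 2 | 2.449 | Φ(0.408) = 0.658 | 0.925 | 0.915 |
| 3 | 3.674 | Φ(0.272) = 0.607 | 0.854 | 0.846 |

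With *d* = 0 the per-child chance is 0.50, and the rule is met with probability 0.613 (n = 12) or 0.623 (n = 10).

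**Integer scores and other readings.** The protocol refers to scores in the plural, so stricter readings were simulated: 100,000 runs, whole-number scores limited to 0–24, assumed true score 12, *s* = 1.5, 2 and 3, n = 10 and 12. With whole numbers, a score equal to the baseline mean does not count as positive, which lowers the no-drift figures.

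| Reading | *d* = 0 | *d* = 1 | *d* = 2 |
|---|---|---|---|
| Post score alone, or mean of the two later scores | 0.43–0.56 | 0.80–0.95 | 0.94 to above 0.99 |
| Both later scores above the baseline mean | 0.06–0.12 | 0.31–0.57 | 0.64–0.97 |

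Taking the continuous and whole-number versions together, the lenient readings run from 0.43–0.62 without drift to 0.80–0.97 with a 1-point drift.

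**The case against.** Several points on the other side carry weight.

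**The scorer is not named.** The text says who conducts sessions, not who scores the answers, when, or from what record. A reader might infer that the person who trained a child also scores that child, unmasked. The document does not support that; it supports only one team doing both jobs. Open-label delivery does not rule out masked scoring, and a condensed article may omit it. The point therefore rests on the stated overlap of roles and the known visit timing, not on silence alone.

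**Drift cannot settle progression alone.** A reader might infer that an inflated strange stories score is enough for an unmodified go. It is not. The primary social competence measure is rated by child and parent, beyond the reach of investigator scoring, and all feasibility outcomes must also be met. The rule also does not say which ToM measure sets the trend.

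**The size is assumed, and the reading matters.** Neither drift nor SD has a source in the document, and the scoring anchors limit a rater's latitude. If both later scores must exceed baseline, a 1-point drift leaves the criterion about as likely to fail as to be met, although several times more likely to be met than without drift.

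**Proportionality.** This is an exploratory pilot with ToM as a secondary outcome. On the lenient reading the rule is met about half the time or more with no effect and no drift. That weakness lies in the threshold, and masking leaves it untouched.

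These points limit the claim. They do not remove the route for bias, which no stated safeguard covers.

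**Conclusion.** The concern stands in limited form. In an open-label study where one team both trains and assesses, the primary measure of change in ToM is a rated verbal response taken at known visits. Scorer expectation after training can push it above the baseline mean.

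With no true effect, *s* of 1.5 to 3 and an assumed 1-point drift, the chance of meeting the 50% ToM criterion rises by roughly 0.25 to 0.50 in absolute terms, whichever reading of the trend rule is used. The direction is secure; the size depends on a drift and an SD that the document does not give. The consequence is bias in the ToM part of the progression rule, not a wrong overall decision by itself. Changing the scoring procedure is worthwhile because it is cheap and would test a method that a larger trial could use.

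**What to change.** 1. Record strange stories answers verbatim at all four visits.
2. Balance the order of the parallel versions across children, so that the version does not reveal the visit.
3. Remove child and visit identifiers and shuffle all time points.
4. After the last follow-up, have an existing investigator who did not assess that child score the batch masked to time point.
5. State that these masked scores determine the ToM trend.

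**Cost.** At most 12 children × 4 visits × 12 stories = 576 short answers to transcribe and code. Scores become available only after follow-up. No extra visits are needed, and no extra staff provided that scoring can be divided so that nobody scores a child they assessed.

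**What remains.** Masked scoring does not remove bias from live administration, such as differences in prompting. Vocabulary learned in training may also hint that an answer came after the intervention.

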### Intervention

A brief overview of the intervention is provided in Table 1. The intervention consists of two phases: an introductory CBT phase (week 1, modules 1 to 3) and an active ToM training phase (weeks 2 to 4, modules 4 to 12). In the introductory CBT phase, children will learn about the relationship between thoughts, feelings and behaviours and complete activities to show that two people can think and feel differently in the same situation and subsequently respond in different ways. They will also complete language exercises focusing on mental state and emotional vocabulary. In the active training phase, children will be introduced to the concept of ToM through three roles/positions: the thinker (understands another person’s thoughts, beliefs and intentions [cognitive ToM]), the feeler (understands another person’s emotional state [affective ToM]) and the responder (can use ToM knowledge to generate an appropriate social response). Strategies to help children take each position will be summarised on self-instructional prompt cards, which will act as a strategy to assist with EF. Children will then be introduced to eight social scenarios that require ToM, in which characters have differing perspectives, beliefs, knowledge or emotional reactions to a situation/event: white lies, misunderstandings, forgetting, irony, pretending, figures of speech, persuasion and double bluff. These scenarios have been selected from the strange stories task, an advanced test of cognitive and affective ToM, for two reasons: (i) children with epilepsy have significant difficulties on this task [5–7] and (ii) a prior ToM intervention found that utilising these specific social scenarios was beneficial for training ToM in children aged 8 to 12 years old [21]. Each subsequent module will focus on one scenario and children will practise applying ToM knowledge and CBT skills to respond. Investigators will provide feedback and prompting to help children modify their performance and generate appropriate responses. Activities will be taught via a variety of mediums including written social stories, videos, role-plays, group discussions and paper and pen tasks. Parents will join children for the final 15 to 30 min of each session, during which a summary of skills will be provided and homework will be allocated. Homework will extend upon the content of intervention sessions. All activities are collated within intervention workbooks, which will be distributed to children and parents on the first day of training. All materials can be accessed by contacting the lead author of this paper.

**Table 1 Tab1:** Brief overview of the intervention

Session^a^	Module	Content
Phase 1. Introductory cognitive behavioural therapy (CBT) phase		
1	1	Thoughts
	2	Feelings
	3	Thoughts, feelings and behaviours
Phase 2. Active Theory of Mind (ToM) training phase		
2	4	Theory of Mind
	5	White lies
	6	Misunderstandings
3	7	Forgetting
	8	Irony
	9	Pretending
	10	Figures of speech
4	11	Persuasion
	12	Double bluff
	13	Review

^a^Session division is a plan only. Content of modules is subject to change based on outcomes of the pilot trial

### Discontinuing/modifying the intervention for individual participants

The intervention has been designed as a comprehensive programme, meaning all children are expected to be able to complete all modules regardless of their baseline cognitive skills (i.e. regardless of whether children are assessed to have impaired language or EF). Nevertheless, investigators will monitor the performance of each child and modify activities, as best as they can, to meet the individual needs of the child during sessions. This individual tailoring is within the scope of investigators’ training and experience as child psychologists and neuropsychologists; in spite of the group setting, we do not anticipate difficulties achieving this individual tailoring, as the group size will be small and multiple investigators will be present for each session. In addition, the intervention may need to be modified or discontinued if (1) an adverse event occurs, including events that are causally related to the intervention, not related or events that have an unidentified cause. Consultation and advice from the governing human research ethics committee (HREC) and (if necessary) from clinicians from participating hospitals and The University of Sydney who are external to the project will be used to determine the most appropriate course of action, or (2) withdrawal of participant consent. Participants will be informed at enrolment and throughout the study that they are free to withdraw at any time without affecting their current or future relationship with treating clinicians, participating hospitals or The University of Sydney. A withdrawal of consent form will be provided with the participant information and consent form (PICF) at the start of the study and will be given to participants at their request (see Additional file 3).

### Fidelity/adherence during the intervention

Homework tasks are optional and no compulsory activities are required of children and parents outside of sessions. Nevertheless, adherence to homework will be monitored by asking parents at the start of each session whether they completed homework activities and recording this information for each child, each week. Although monitoring adherence/fidelity is important, particularly when assessing whether adherence to certain aspects of treatment affects outcomes in a trial, the primary objective of this study is to assess feasibility of the intervention. We are primarily interested in whether homework is perceived to be beneficial, achievable and relevant for families. Failure to complete homework or feedback that activities are irrelevant or too time-consuming will be used along with other information as a measure of treatment acceptability.

